### Safety outcomes

All variables related to the safety assessment, such as vital signs, physical examinations, laboratory tests (complete blood cell count, liver function test, renal function test) and adverse events (AEs) will be documented on the case report form (CRF) at every visit.

### Statistical analysis

#### Efficacy assessment

Statistical analyses will be performed for both the ITT (intention-to treat, all randomly assigned participants) and PP (per-protocol, participants completed the trial without any protocol deviations) data sets. The missing values will be imputed by the last observation carried forward (LOCF) method. The continuous variables will be displayed as the mean ± SD(standard deviation), and the categorical variables will be displayed as the n (%). The baseline characteristics will be compared by either a Student’s *t*-test for continuous variables or the χ^2^ test (Fisher’s exact test will be used when the expected value is < 5) for the categorical data. Alternatively, McNemar’s test will be used if the normality assumption is not satisfied for the continuous variables. For the primary outcome measures, the mean differences from the baseline values to the end of treatment will be compared using an independent T-test.

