### Subject withdrawal criteria

The subjects who meet the criteria listed in Subject withdrawal criteria section will be discontinued from treatment. The participants who are withdrawn after randomisation will be followed for outcomes.

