### Primary outcome measurement

The primary outcome in the present study is the change in the SCORAD index between the baseline (Visit 2) and after the treatment (Visit 5). The SCORAD index is a clinical tool for assessing the severity of atopic dermatitis as objectively as possible. The SCORAD index will be measured at every visit.

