### Secondary outcome measurement

Secondary outcome measurements include the change in the Dermatology Life Quality Index (DLQI), the total IgE level, eosinophil counts, IL-4, IL-5, IL-13, TEWL (Transepidermal Water Loss), hydration in the stratum corneum, and KiFDA-HM-AD. The study schedule is detailed in Table 1.

**Table 1 T1:** Study schedule of KM110329 clinical trial (8 weeks)

	**Screening**	**Treatment period**			
	**Visit 1**	**Visit 2**	**Visit 3**	**Visit 4**	**Visit 5**
	**(D − 7)**	**(D 0)**	**(D 7)**	**(D 28)**	**(D 56)**
**Informed consent**	**√**				
**Demographic characteristic eristic**	**√**				
**SCORAD index**	**√**	**√**	**√**	**√**	**√**
**Dermatology Life Quality Index**		**√**	**√**	**√**	**√**
**KiFDA-HM-AD**		**√**	**√**	**√**	**√**
**Laboratory tests**^ **1** ^	**√**	**√**			**√**
**Test for chronic hepatitis**^ **2** ^	**√**				
**Drug use history**	**√**				
**Concomitant medication**	**√**	**√**	**√**	**√**	**√**
**Pregnancy test**	**√**	**√**	**√**	**√**	**√**
**Medical/drug use history**	**√**	**√**	**√**	**√**	**√**
**Adverse event**			**√**	**√**	**√**
**Compliance calculation**			**√**	**√**	**√**
**Inclusion/exclusion criteria check**	**√**				
**Randomisation**		**√**			

^1^CBC (RBC, Hb, Hct, WBC, Platelet, ESR), Immunological tests (Eosinophil, IgE, IL-4, IL-5, IL-13), Liver function tests (AST, ALT), Renal function tests (BUN, Creatinine).

^2^Anti-HBs, HBsAg.

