#### Safety assessment

All participants will report any adverse events that they experience while undergoing the intervention at every visit. Every adverse event will be described in the CRF. If the adverse event is severe and associated with the trial, the participant will be withdrawn from the trial, and the appropriate treatment will be given to him or her. For the safety assessment, a liver function test, blood cell count test and physical examination will be performed at Visits 1, 2 and 5. The safety-related variables will be analysed using the ITT method.

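### LOCF is the only method named for missing efficacy values: it can bias the 8-week SCORAD contrast in either direction, and it gives zero change on the immunological outcomes when Visit 5 is missing

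*Protocol article*

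**What the plan says.** The Efficacy assessment section fixes the method in one sentence: "The missing values will be imputed by the last observation carried forward (LOCF) method". No alternative or sensitivity analysis is named. The same section defines the analysis sets as "ITT (intention-to treat, all randomly assigned participants) and PP (per-protocol, participants completed the trial without any protocol deviations", so imputed values act in the ITT set.

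The primary outcome is "the change in the SCORAD index between the baseline (Visit 2) and after the treatment (Visit 5", and for it "the mean differences from the baseline values to the end of treatment will be compared using an independent T-test". On timing, "The SCORAD index will be measured at every visit"; Table 1 places the visits after screening at days 0, 7, 28 and 56.

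The immunological secondary outcomes come under the laboratory tests, whose footnote in Table 1 lists "Immunological tests (Eosinophil, IgE, IL-4, IL-5, IL-13". Table 1 ticks laboratory tests at Visits 1, 2 and 5 only. The Safety assessment section gives the same visits for the safety tests that it names: "a liver function test, blood cell count test and physical examination will be performed at Visits 1, 2 and 5". The Abstract (Methods/design) and the Safety outcomes section instead speak of every visit. I follow Table 1 because the article names it as the detailed schedule.

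The Subject withdrawal criteria section adds: "The participants who are withdrawn after randomisation will be followed for outcomes".

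**The concern.** LOCF assumes that a participant's condition stays fixed from the last visit to day 56. In an 8-week trial that looks for continuing improvement, this is hard to defend. Someone last seen on day 7 keeps a one-week result, and someone lost before Visit 3 keeps the baseline score and so has no change at all. The t-test then counts these values as if they had been observed.

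If the arms lose participants at different rates or times, the error does not cancel. It can dilute a real effect, inflate one, or create a difference where none exists, so LOCF cannot be defended as conservative.

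The immunological outcomes are a sharper case. Visit 5 is their only post-baseline measurement, so the value carried forward is the Visit 2 baseline.

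**Working it through.** **Inputs from the protocol.** Sample size section: difference 10, SD 13.576, 80% power, 5% two-sided significance, 10% dropout. Table 1: SCORAD on days 0, 7, 28 and 56; laboratory tests at Visits 1, 2 and 5.

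**The plan's own figure.** n = 2(z_α/2 + z_β)²σ²/Δ². Unrounded z-values give the printed 28.932; the rounded 1.96 and 0.84 give 28.90. Either rounds up to 29, and 29/0.9 = 32.2, so 33 per group. The figure reproduces. With 10% lost, about 30 per group remain and t-test power is about 80%; with all 33 observed it is about 84%.

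**Assumptions of mine, not in the protocol.** Improvement is linear over 56 days. Participants without Visit 5 were last seen at Visit 3 or Visit 4 in equal numbers. Placebo improves by 0 or 10 points. A carried-forward change has either the full 8-week SD or a variance that grows in proportion to time.

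**Formula.** Let m be an arm's true mean 8-week improvement, d its share without Visit 5, and f the share of that improvement reached at the last observed visit. The expected LOCF change is m[(1 − d) + d·f] = m[1 − d(1 − f)]. Here f averages (7/56 + 28/56)/2 = 0.3125, so 1 − f = 0.6875.

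**SCORAD, true difference 10.**
- 10% in both arms: each arm is multiplied by 1 − 0.1 × 0.6875 = 0.931, so 10 becomes 9.3. If dropouts have only a baseline value (f = 0) it becomes 9.0; if all were last seen on day 28 (f = 0.5), 9.5; if they had already reached their 8-week change (f = 1), it stays 10.0.
- 15% active, 5% placebo, improvements 20 and 10: 20 × 0.8969 − 10 × 0.9656 = 8.3. With improvements 10 and 0: 10 × 0.8969 = 9.0.
- 20% in placebo only, improvements 20 and 10, f = 0: 20 − 10 × 0.8 = 12.0. Here the effect is inflated.

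**Power by simulation** (33 per arm, 40,000 runs, range over the two variance assumptions).

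| Dropout active/placebo | Placebo change | LOCF difference | Power |
|---|---|---|---|
| 10% / 10% | 10 | 9.3 | 76–79% |
| 10% / 10% | 0 | 9.3 | 78–81% |
| 15% / 5% | 10 | 8.3 | 65–68% |
| 15% / 5% | 0 | 9.0 | 75–78% |

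**No true effect, 10-point improvement in both arms.**
- Equal dropout with equal timing: bias 0.
- 5% vs 15%: 10 × 0.10 × 0.6875 = 0.7 points; type I error about 5.5%.
- 0% vs 20%: 10 × 0.20 × 0.6875 = 1.4 points, type I error about 7%. With f = 0, 2.0 points and about 10%.

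**Immunological outcomes.** With Visit 5 missing, the imputed change is Visit 2 − Visit 2 = 0, so f = 0 whatever the dropout pattern. At 10% missing in both arms the expected group difference is multiplied by 0.9. At most about 0.1 × 33 = 3.3 participants per arm are affected, fewer if some of those who withdraw are still seen at Visit 5.

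**The case against.** The strongest defence is that the damage is small at the planned dropout. With equal 10% loss, LOCF gives 76–81% power against a planned 80%, and the estimate falls by under one point. The larger losses need unequal dropout, and the lowest power also needs a 10-point placebo improvement that the protocol does not give. Setting that case against the 84% for complete data would overstate the loss, because the sample size already allows for dropout. All of this stands. What it leaves untouched is that the direction of the bias is not controlled.

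A reader might infer four stronger things that the document does not support.
- *Every dropout gets zero change on the immunological outcomes.* Withdrawn participants are to be followed, and LOCF fills only missing values. The point covers those without a Visit 5 value.
- *LOCF overwrites values observed after withdrawal.* Nothing says so. The article merely does not state that they are used.
- *Baseline liver or renal values are carried forward and hide harm.* The LOCF sentence stands under Efficacy assessment. Safety assessment refers only to an ITT method, and ITT is defined as a population, not an imputation rule. The scope is unclear, no more.
- *The zero-change problem covers all secondary outcomes.* DLQI and KiFDA-HM-AD are measured at Visits 2 to 5, and TEWL and hydration do not appear in Table 1.

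The point is also not one to leave to an unseen analysis plan, because the protocol itself fixes the method.

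**Conclusion.** The point holds for the efficacy outcomes and should be corrected. For SCORAD the bias is conditional: it vanishes if leavers had already reached their 8-week change, or if there is no effect and dropout is alike in both arms. Otherwise it may favour either arm. Under the stated assumptions a true 10 points becomes about 9.3 at the planned dropout and 8.3–9.0 at 15% vs 5%. A spurious 1.4–2.0 points can appear at 0% vs 20%.

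For the five immunological outcomes, zero change for a missing Visit 5 follows directly from the schedule. It rests only on Table 1 prevailing over the general statements that measurements are made at every visit.

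**What to change.** - Replace LOCF as the primary method with a mixed model for repeated measures on SCORAD at Visits 3, 4 and 5, adjusted for baseline SCORAD, with the Visit 5 difference as the primary contrast.
- State that every observed Visit 5 value is used, including those collected after withdrawal.
- For outcomes with a single post-baseline value, use a baseline-adjusted analysis of observed values or multiple imputation.
- Keep LOCF at most as a sensitivity analysis.
- State that safety laboratory values are shown as observed, and align the every-visit wording in the Abstract and Safety outcomes with Table 1.

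The cost is a change of wording and modest programming. No new visits, data or participants are needed, since the intermediate SCORAD values are already scheduled. The downside is a slightly more complex primary model than a t-test.

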## Methods/design

A randomised, double blind, placebo-controlled, multicentre trial will be conducted at the Seoul St. Mary’s Hospital, Chung-ang University Hospital, and Kyung Hee University Hospital in Gangdong. Participants fulfilling the eligibility criteria will be selected. The enrolled participants will be randomly allocated to two parallel groups corresponding to the KM110329 and placebo arms. Each participant will be examined for signs and symptoms of AD before and after taking the functional food. Figure 1 shows the schematic flow of the study.

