### Sample size

Sample size calculations were performed to determine the number of participants needed to detect the effect sizes. We obtained an effect size from the previous study and based on the agreement of experts [14]. The results from the previous study were used to calculate the standard deviation [15]. The mean difference and standard deviation of the scoring atopic dermatitis (SCORAD) index were 10 and 13.576, respectively. The following formula was used to estimate the sample size.

$$\begin{array}{ll} n & =\frac{2{\left(z_{\alpha /2}+z_{\beta }\right)}^{2}\sigma^{2}}{{\left(\mu_{c}-\mu_{t}\right)}^{2}}\\ & =\frac{2\times {\left(1.96+0.84\right)}^{2}\times 13.576^{2}}{10^{2}}\\ & =28.932 \end{array}$$

The calculation was performed using 80% power, a 5% significance level, and a 10% dropout rate. The required sample size is approximately 33 participants for each group. Therefore, a total of 66 participants are needed for this trial.

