### Randomisation and allocation

The study subjects who satisfy the eligibility criteria will be randomised using a computer program at an independent centre (Kyung Hee University Center for Clinical Research and Drug Development; KCRD). Block randomisation with block size of 4 will be performed. The study subjects will be assigned to one of two groups with a 1:1 allocation ratio by investigator in each study site. Random numbers will be sent to each centre, and a randomisation table will be maintained by KCRD during the research period. Opaque sealed envelopes containing serial numbers will be delivered to each centre. The randomisation table kept in an opaque sealed envelope by the contract research organisation (CRO; KCRD) should be opened according to Standard Operating Procedures (SOPs).

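### The stated fallback for non-normal continuous variables, McNemar's test, cannot compare a continuous variable between two independent arms

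*Protocol article*

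**What the plan says.** The design is parallel-group: "The enrolled participants will be randomly allocated to two parallel groups corresponding to the KM110329 and placebo arms". Participants are "assigned to one of two groups with a 1:1 allocation ratio".

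Under Statistical analysis, Efficacy assessment, the text runs in this order:

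1. Continuous variables are summarised by mean and SD, categorical variables by count and percentage.
2. "The baseline characteristics will be compared by either a Student’s" t-test if continuous, or by the chi-squared test (Fisher's exact test when expected counts are small) if categorical.
3. "Alternatively, McNemar’s test will be used if the normality assumption is not satisfied for the continuous variables".
4. For the primary outcome, "the mean differences from the baseline values to the end of treatment will be compared using an independent T-test".

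The article gives no other rule for non-normal data: no rank test, no transformation, no resampling method. The Secondary outcome measurement section lists changes in the DLQI and in "the total IgE level, eosinophil counts, IL-4, IL-5, IL-13, TEWL (Transepidermal Water Loss), hydration in the stratum corneum, and KiFDA-HM-AD". The Efficacy assessment section names no separate test for these outcomes.

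**The concern.** McNemar's test asks whether two paired binary proportions differ. The sentence assigns it to continuous variables in a trial whose comparisons are between two unpaired groups, so the data meet neither of its requirements.

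A fallback is written in advance so that the choice of test does not depend on the results. If the named test cannot be run, whoever analyses the data must choose another once the data are in hand. If instead the rule is followed literally by making the data binary and paired, the resulting p-value answers a different question from the one the trial asks.

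**Working it through.** **What the test needs.** McNemar's statistic is (b − c)² / (b + c), where b and c are the two discordant counts in a 2×2 table of matched pairs. It requires a binary variable and two linked observations per pair.

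**What each possible reading supplies.**

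| Reading of the sentence | Binary? | Paired? | Result |
|---|---|---|---|
| Continuous baseline variable, KM110329 versus placebo | No | No | b and c do not exist; the test cannot be computed |
| Continuous outcome or its change, KM110329 versus placebo | No | No | As above |
| Continuous variable, before versus after within one arm | No | Yes | Still not computable without a cut-point |
| Dichotomised variable, before versus after within one arm | Yes | Yes | Computable, but no comparison of the arms; the article gives no cut-point |

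No reading gives a valid between-arm comparison of a continuous variable.

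**Which variables the sentence covers.** Two features point to the baseline variables alone: it comes straight after the baseline tests, and its opening word offers an alternative to them. Three features allow a wider reading: the subsection is about efficacy, the sentence refers to continuous variables without restriction (as the sentence on summary statistics does), and it is the only non-normality rule. Baseline coverage is therefore the minimum. Coverage of the secondary outcomes is possible but not established.

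**Does it touch the sample size?** The Sample size section states: "The mean difference and standard deviation of the scoring atopic dermatitis (SCORAD) index were 10 and 13.576, respectively". It adds: "The calculation was performed using 80% power, a 5% significance level, and a 10% dropout rate".

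- The printed formula with rounded z values gives 2 × (1.96 + 0.84)² × 13.576² / 10² = 28.90. The printed 28.932 corresponds to unrounded z values, a trivial difference. Both round up to 29 per arm.
- With 10% dropout: 29 / (1 − 0.10) = 32.2, rounded up to 33 per arm, and 2 × 33 = 66 in total.

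The plan's figures reproduce. They rest on a two-sample comparison of means and do not involve McNemar's test.

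**What a valid fallback would cost in power (for scale only).** Assume that a rank-sum test is applied to data that are in fact normal, with asymptotic relative efficiency 3/π = 0.955, and take the SCORAD planning values. Then 29 evaluable per arm act like 29 × 0.955 = 27.7. Power on the normal approximation is about 78%, against 80% for the t-test.

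**The case against.** The strongest counter-argument concerns reach. The sentence most naturally modifies the baseline tests, and baseline comparisons in a randomised trial decide nothing about efficacy. A test that cannot be run would also be noticed and replaced, so a wrong published result is less likely than a fallback chosen late. Both points stand, and they limit the seriousness of the error.

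A reader might infer more than the article supports, in four ways:

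- **That the primary analysis is affected.** It is not. The SCORAD change has its own sentence naming an independent t-test, with no normality condition attached.
- **That the rule definitely governs the secondary outcomes.** This is open. The absence of a named test for them may be filled by an analysis plan or full protocol that is not shown, and that absence is not itself a fault.
- **That the laboratory outcomes must be skewed because they cannot fall below zero.** The secondary outcomes are defined as changes, which can be negative, and the article gives no distributional data.
- **That the efficiency loss from a median split measures the harm.** The plan proposes no dichotomisation, so such a figure does not describe it.

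It could also be said that an article condenses its protocol and that details belong in the analysis plan. That does not answer this point. The article does not leave the test out; it names one that does not fit, and an analysis plan naming a valid test would contradict it.

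**Conclusion.** The stated rule is wrong as written: McNemar's test cannot compare a continuous variable between the two independent arms, and the article offers no valid fallback. This follows from the definition of the test and the parallel-group design, and needs no assumption about the data.

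The practical size depends on scope. If the sentence covers baseline variables only, the effect is small. If it also covers the continuous secondary outcomes, the article fixes no workable method for any of them that proves non-normal. Under either reading, the primary SCORAD comparison and the sample size of 66 are unaffected. The sentence should be corrected, but the trial's main conclusion does not depend on it.

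**What to change.** Replace the sentence with wording along these lines: *Where a continuous variable does not satisfy the normality assumption, the two arms will be compared with the Wilcoxon rank-sum (Mann-Whitney) test.* Add a statement of whether the rule covers the baseline variables only or also the continuous secondary outcomes.

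The analysis plan, if there is one, should say the same. The cost is one or two sentences, with no change to data collection, patient burden or sample size. The change should be made before unblinding, so that the fallback remains prespecified.

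### The primary t-test on SCORAD change is valid but fixes the baseline slope at 1; adjusting for Visit 2 SCORAD would be more precise at no extra data cost

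*Protocol article*

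**What the plan says.** Under Primary outcome measurement, the protocol article defines the endpoint as the SCORAD change from Visit 2 (baseline) to Visit 5 (week 8), and adds: "The SCORAD index will be measured at every visit". Baseline SCORAD is therefore already in hand for everyone randomised.

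Under Efficacy assessment, the primary comparison is fixed: "the mean differences from the baseline values to the end of treatment will be compared using an independent T-test". No covariate is named. The same paragraph has baseline characteristics compared by significance tests, but no later step uses the result.

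Under Randomisation and allocation, patients are "assigned to one of two groups with a 1:1 allocation ratio", and "Block randomisation with block size of 4 will be performed". Stratification by baseline severity is not stated.

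Under Sample size: "The mean difference and standard deviation of the scoring atopic dermatitis (SCORAD) index were 10 and 13.576, respectively". The calculation uses "80% power, a 5% significance level, and a 10% dropout rate" and arrives at 33 per group, 66 in all. The section does not say whether 13.576 is the SD of change or of a single score.

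**The concern.** A change score uses the baseline only by subtraction. That amounts to assuming that each extra point of SCORAD at Visit 2 predicts exactly one extra point at Visit 5. If the true slope is below 1, subtraction over-corrects: change stays correlated with baseline, and that correlation remains as avoidable noise. ANCOVA estimates the slope instead of fixing it.

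Two things are at stake. One is precision, in a trial planned for only 33 per arm. The other is the reading of the result if the arms happen to differ at baseline, since part of that difference is carried into the estimate and nothing in the stated design balances SCORAD. If adjustment were added only after such an imbalance had been seen, it would be open to challenge as post hoc.

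**Working it through.** **Inputs from the protocol article.** Difference 10; SD 13.576; two-sided 5%; 80% power; 10% dropout; 33 per group. Evaluable per arm: 33 × 0.9 = 29.7.

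**Inputs assumed.** Baseline-to-week-8 correlation ρ, from 0.3 to 0.9. Baseline SD where variances are not taken as equal: 8.

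**The plan's own figure.** n = 2(z₀.₉₇₅ + z₀.₈₀)² × 13.576² / 10² = 28.93 with unrounded z values (28.90 with the printed 1.96 and 0.84). Rounded up this is 29, and 29 / 0.9 = 32.2, so 33 per group and 66 in total. The plan's figure reproduces.

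**Method for power.** Noncentral t, 29.7 per arm, difference 10, with one degree of freedom given up for the covariate under ANCOVA.

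**Reading A: 13.576 is the SD of change, equal variances at both visits.** With score variance s², Var(change) = 2s²(1 − ρ) and Var(ANCOVA residual) = s²(1 − ρ²). The ratio is (1 + ρ)/2, so the ANCOVA SD is 13.576 × √((1 + ρ)/2).

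| ρ | Variance ratio | ANCOVA SD | Power, t-test | Power, ANCOVA |
|---|---|---|---|---|
| 0.3 | 0.65 | 10.95 | 79.7% | 93.3% |
| 0.5 | 0.75 | 11.76 | 79.7% | 89.6% |
| 0.7 | 0.85 | 12.52 | 79.7% | 85.7% |
| 0.9 | 0.95 | 13.23 | 79.7% | 81.7% |

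**Reading A without equal variances.** With baseline SD s_x and slope b, the residual variance is 13.576² − s_x²(1 − b)², where 13.576² = 184.31. For s_x = 8:

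| b | Residual variance | ANCOVA SD | Power, ANCOVA |
|---|---|---|---|
| 0.3 | 184.31 − 31.36 = 152.95 | 12.37 | about 86% |
| 0.5 | 184.31 − 16.00 = 168.31 | 12.97 | about 83% |
| 0.7 | 184.31 − 5.76 = 178.55 | 13.36 | about 81% |

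**Reading B: 13.576 is the SD of a single score, equal variances.** SD of change = 13.576 × √(2(1 − ρ)); ANCOVA SD = 13.576 × √(1 − ρ²).

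| ρ | SD of change | Power, t-test | ANCOVA SD | Power, ANCOVA |
|---|---|---|---|---|
| 0.3 | 16.06 | 65.5% | 12.95 | 83.3% |
| 0.5 | 13.58 | 79.7% | 11.76 | 89.6% |
| 0.7 | 10.52 | 95.0% | 9.70 | 97.4% |

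**Chance imbalance.** The SE of the baseline difference at 33 per arm is √(2/33) = 0.246 score SDs. With equal variances, ρ = 0.5 and a change SD of 13.576, the score SD is 13.576 / √(2 × 0.5) = 13.6, so 1 SE is 0.246 × 13.6 = 3.3 points. The change-score estimate then shifts by (1 − 0.5) × 3.3 = 1.7 points, given that this imbalance occurs. With a baseline SD of 8 and slope 0.5, the 1-SE shift is 0.5 × 8 × 0.246 = 1.0 point. The target difference is 10.

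**The case against.** The strongest reply is that nothing here is an error. In a 1:1 randomised trial the t-test on change is unbiased over randomisations, holds its 5% level, and has a standard error that already includes chance imbalance. The sample size formula matches the planned test and reproduces. On this view the point is only a preference for a more efficient method. The facts in this reply all stand. They limit the point to precision and to how the result reads after an imbalance, but they do not remove it: the article itself fixes the less precise test, so the choice has not been left to an unseen analysis plan.

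The reply is also right that the gain could be modest. The equal-variance model needs a baseline SD of 13.576 / √(2 × 0.3) = 17.5 at ρ = 0.7, whereas a uniform spread over 0 to 40 has an SD of 40/√12 = 11.5. The entry cap of 40 is on objective SCORAD and the endpoint is the SCORAD index, so this is indicative only, but it makes the smaller gains plausible.

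A reader might infer several stronger claims that the document does not support:

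- **The planned result would be biased or its error rate wrong.** The shift is conditional on an imbalance that has occurred; averaged over randomisations it is zero.
- **A baseline difference passes whole into the estimate.** Only (1 − slope) of it does.
- **The baseline is thrown away.** It is used, by subtraction.
- **The baseline significance tests are meant to protect the primary analysis.** The article presents them only as a comparison of characteristics.
- **The secondary outcomes share the fault.** The article fixes this test for the primary outcome only.

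**Conclusion.** The point holds as one of efficiency, not validity. Under every scenario computed, ANCOVA has more power than the planned test. Its advantage runs from about 1 percentage point (baseline SD 8, slope 0.7) through about 10 points (ρ = 0.5, equal variances) to about 18 points (13.576 as a single-score SD, ρ = 0.3). Only in that last case does the planned test fall well short of the intended 80%, at 65.5%, while ANCOVA meets it.

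That ANCOVA is the better choice is firm; how much better is not. The figures rest on an assumed correlation or slope, an assumed baseline SD, an unresolved reading of 13.576, and the plan's 10% dropout. The 66-patient total is not in question if 13.576 is the SD of change. This is a change that should be made, not one on which the trial's validity depends.

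**What to change.** Before unblinding, replace the primary t-test with an ANCOVA of Visit 5 SCORAD on treatment, with Visit 2 SCORAD as covariate. Modelling change with the same covariate gives the same treatment estimate, so the endpoint definition can stay. Report the adjusted mean difference with its 95% CI, and keep the t-test on change as a sensitivity analysis. State under Sample size whether 13.576 is the SD of change or of a single score.

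The cost is wording only: no new data, visits or patients.
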